### 2.5. Diet Quality 

To collect dietary data, the semi-quantitative food frequency method will be applied, and a food frequency questionnaire (KomPAN) will be used. The KomPAN questionnaire consists of 46 food items and includes a comprehensive variety of foods usually consumed in Poland [30]. The KomPAN questionnaire has been assessed in healthy/unhealthy subjects as reliable tools with acceptable to very good reproducibility [30,31]. To assess diet quality, two predefined diet quality scores (the a priori approach) will be used: pro-Healthy-Diet-Index (pHDI) and non-Healthy-Diet-Index (nHDI).

Participants will be asked to indicate the average frequency of consumption of each food item over the 12 last months. Enrolled participants will receive a questionnaire from trained researchers, who will provide guidance and assistance as required on a one-to-one basis. 

To indicate food frequency consumption, respondents will choose one of six categories (converted into daily frequency): ‘never’ (0 times/day), ‘1–3 times a month’ (0.06 times/day), ‘once a week’ (0.14 times/day), ‘few times a week’ (0.5 times/day), ‘once a day’ (1.0 time/day), or ‘few times a day’ (2.0 times/day) [31]. Daily frequencies of 24 food items will be used to calculate pHDI and nHDI. The pHDI includes 10 food items: wholemeal bread/bread rolls, coarse-ground groats, milk, fermented milk drinks, cheese curd products, white meat, fish, legumes, fruit, and vegetables. The nHDI includes 14 food items: white bread and bakery products, white rice and fine-ground groats, fast foods, fried foods, butter, lard, cheese, cured meat/smoked sausages/hot dogs, red meat, sweets, tinned meats, sweetened carbonated or still drinks, energy drinks, and alcoholic beverages. Daily frequencies of the consumption of the selected 10 (pHDI) or 14 (nHDI) food items will be summed up and recalculated into a range of 0%–100% points according to the questionnaire’s manual [30]. A higher percentage of points reflected greater adherence to the diet quality score, i.e., for pHDI – better diet quality and for nHDI – worse diet quality.

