#### 3.1.2. Foods Rich in Calcium

For foods rich in calcium (e.g., milk, fermented milk drinks, curd cheese, cheese), the recommended consumption frequency is several times a day, which is in line with the recommendation for the general population [27,28,29]. Calcium deficiencies can have serious consequences for the health of women with hypothyroidism. The main role of thyroid hormones is metabolism regulation, but it also participates in bone tissue reconstruction. One consequence of hypothyroidism is a reduction in the processes of bone tissue reconstruction resulting from the inhibition of bone mineralization. Therefore, the diet of patients with hypothyroidism should be rich in dietary calcium, such as milk, yoghurt, cheese, low-, regular-, or high-fat dairy, and small fish eaten along with bones [47]. Some studies on HT have focused on lactose intolerance diagnosed with an elimination diet, hydrogen tests, lactose tolerance tests, or small intestinal biopsies [16]. It was found that 75% out of 84 patients with HT, all of whom were residents of the Mediterranean Sea region and Turkey, had lactose intolerance. Asik et al. [48] found that lactose elimination from the diet of HT patients decreased the TSH level without a modification dose of levothyroxine. For this reason, the authors suggested that patients demonstrating great fluctuations in the concentration of TSH while taking a steady dose of levothyroxine should be tested for lactose intolerance.

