**Exclusion Criteria**: non-Hashimoto thyroiditis; pregnant or breastfeeding women; current/past use of dietary supplements, e.g., selenium or iodine; current use of other supplements in an amount above an upper level; diagnosed presence of other comorbidities: other endocrinopathy and metabolic diseases (e.g., diabetes, cardiovascular diseases), other thyroid diseases with chronic inflammation, diseases requiring an elimination diet (e.g., celiac disease, non-celiac gluten sensitivity, food allergy, food intolerance, etc.); other special diet with or without disease diagnosis lasting >4 months within the last 12 months: rigorous elimination diet (e.g., gluten-free, lactose-free), unbalanced diet (e.g., high protein, ketogenic), low-energy diet with an energy restriction >1000 kcal/day, very low-energy diet (e.g., liquid meal replacements), so-called ‘the autoimmune protocol’ and others that significantly change metabolism; underweight (BMI <18.5 kg/m^2^) or obesity with BMI ≥35 kg/m^2^; weight loss >4 kg in the last month.

**Table 3 ijerph-16-04841-t003:** The qualitative dietary protocol: (A) Self-monitoring diary for recommended foods.

Foods Recommended for Consumption Control the Frequency of the Food Consumption Every Meal/Eating Episode (or at least Every Day) and Check Adherence to Recommendations. Minimum Frequencies Are Indicated.							
Day	Vegetables (see diary B)	Foods rich in calcium e.g., milk, fermented milk drinks, curd cheese, cheese	Fruit	Whole grains e.g., buckwheat grain, wholemeal wheat and rye bread	Animal foods rich in zinc e.g., meats: beef, lamb, pork; eggs	Animal foods rich in selenium e.g., fish, seafood	Nuts and seeds e.g., nuts, pumpkin seeds, sunflower seeds
	Several times a day	Several times a day	Once a day	Once a day	Several times a week	Several times a week	Several times a week
Month: **Mark** ✕ **each time after food consumption**							
1							
2							
3							
…							
31							
*Month: June 2019 **Sample record of the Patient***							
*1*	✕✕	✕	✕✕	✕		✕	
*2*	✕✕✕	✕	✕	✕	✕	✕	
*3*	✕	✕✕✕	✕	✕		✕	
*4*	✕	✕✕		✕	✕	✕	
*5*	✕✕✕	✕	✕	✕	✕	✕	
*6*	✕✕	✕✕				✕	
*7*	✕✕✕	✕✕	✕		✕		

**Table 4 ijerph-16-04841-t004:** The qualitative dietary protocol: (B) Self-monitoring diary for foods with limited consumption.

Foods with Limited Consumption Control the Frequency of the Food Consumption Every Meal/Eating Episode (or at least Every Day) and Check Adherence to Recommendations. Maximum Frequencies Are Indicated.						

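### Two of the 14 nHDI items, cheese and red meat, count as worse diet although the tested protocol names them as recommended foods, so adherence met through them can offset the gain in this outcome.

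*Protocol article*

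**What the plan says.** Section 2.5 defines two diet-quality scores, pHDI and nHDI. On the second it says "The nHDI includes 14 food items", and the list includes "butter, lard, cheese, cured meat/smoked sausages/hot dogs, red meat, sweets, tinned meats". A higher score is read as follows: "for pHDI – better diet quality and for nHDI – worse diet quality". On scoring, the daily frequencies of the selected "food items will be summed up and recalculated into a range of 0%–100% points according to the questionnaire’s manual". The six answer categories carry 0, 0.06, 0.14, 0.5, 1.0 and 2.0 times per day.

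Table 3 (List A, recommended foods) has a column "Foods rich in calcium e.g., milk, fermented milk drinks, curd cheese, cheese", to be eaten several times a day, and a column "Animal foods rich in zinc e.g., meats: beef, lamb, pork; eggs", to be eaten several times a week. The table header marks these frequencies as minimums. Section 3.1.2 repeats the first: "For foods rich in calcium (e.g., milk, fermented milk drinks, curd cheese, cheese), the recommended consumption frequency is several times a day". Section 3.1.5 repeats the weekly frequency for zinc-rich animal foods. Under Section 2.4, each recommendation met earns one point of the 0–13 adherence score.

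Diet quality is part of the third aim (Section 1.1). Section 2.12 plans tests of change in the diet-quality scores and a logistic model for high diet quality. Section 3.3 concedes that the questionnaire is not thyroid-specific and lacks detail on some foods. It does not say that two items are scored against the recommendations.

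**The concern.** The outcome and the intervention point in opposite directions for two foods. A serving of cheese or pork can count towards adherence and also count as a worse diet. For calcium, equally adherent women are treated differently: milk, fermented milk and curd cheese add to pHDI, while cheese adds to nHDI. For zinc, three of the four foods named in Table 3 are red meats in ordinary usage, and the fourth, eggs, is in neither index.

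Improved diet quality is also the route by which Section 1.1 expects gains in quality of life, adiposity and metabolic parameters. If nHDI fails to fall, the plan as written cannot show whether the counselling failed or the score penalised women for following it.

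**Working it through.** The plan gives no figure to reproduce here. The check compares the items and then applies the stated weights to illustrative diet changes.

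**Items compared**
- In nHDI and recommended in List A: cheese, red meat (2 of 14).
- In nHDI and limited by List B (Table 4): sweets, sweetened drinks, energy drinks, fast foods, alcohol. Table 4 also names deep-fried foods under fast foods, and fried foods are a separate nHDI item.

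**Inputs**
- Weights from Section 2.5: 1–3 times a month 0.06, once a week 0.14, few times a week 0.5, once a day 1.0, few times a day 2.0.
- Assumed rescaling: nHDI = 100 × sum / (14 × 2.0) = 100 × sum / 28.
- Assumed matching of categories: several times a day = 2.0, several times a week = 0.5, List B's once a month = 0.06.
- Starting diets are illustrative.

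**Effect of List A through the two foods**
- Cheese, weekly to few times a day: (2.0 − 0.14)/28 = +6.64 points.
- Cheese, weekly to once a day: (1.0 − 0.14)/28 = +3.07.
- Cheese, few times a week to few times a day: (2.0 − 0.5)/28 = +5.36.
- Cheese, few times a week to once a day: (1.0 − 0.5)/28 = +1.79.
- Red meat, weekly to few times a week: (0.5 − 0.14)/28 = +1.29.

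**Effect of List B**
- Sweets 1.0 → 0.14: −3.07.
- Sweetened drinks 0.5 → 0.14: −1.29.
- Fast foods 0.5 → 0.14: −1.29.
- Alcohol 0.14 → 0.06: −0.29.
- Total: −1.66/28 = −5.93.

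**Net change for a woman who follows both lists**

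| How List A is met | Change in sum | Net nHDI |
|---|---|---|
| Milk and eggs | −1.66 | −5.93 |
| Cheese 0.5 → 1.0, red meat 0.14 → 0.5 | 0.50 + 0.36 − 1.66 = −0.80 | −2.86 |
| Cheese 0.14 → 1.0, red meat 0.14 → 0.5 | 0.86 + 0.36 − 1.66 = −0.44 | −1.57 |
| Cheese 0.5 → 2.0, red meat already 0.5 | 1.50 − 1.66 = −0.16 | −0.57 |
| Cheese 0.5 → 2.0, red meat 0.14 → 0.5 | 1.50 + 0.36 − 1.66 = +0.20 | +0.71 |
| Cheese 0.14 → 2.0, red meat 0.14 → 0.5 | 1.86 + 0.36 − 1.66 = +0.56 | +2.00 |

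If fried foods also fall from 0.5 to 0.14, every row drops by a further 0.36/28 = 1.29, so +0.71 becomes −0.57.

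**Without the two items** the maximum is 12 × 2.0 = 24. The same List B changes then give −1.66/24 = −6.92 in every row, whichever List A foods are chosen.

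**The case against.** The case for leaving the plan alone has several sound parts.

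- The List A entries are examples. The minimum applies to the food group, not to cheese or red meat. Milk, fermented milk or curd cheese meets the calcium item and raises pHDI, and eggs meet the zinc item. None of these raises nHDI.
- The sign of the net change depends on the chosen inputs. Starting from the +0.71 row, it turns negative if cheese rises only to once a day, if red meat is already eaten a few times a week, or if fried foods fall. The second is plausible, since Section 3.1.5 says the Polish population tends to eat too much red and processed meat.
- Only two items conflict, and more than two agree with List B. Overall quality of life and BMI, not nHDI, set the sample size (Section 2.11).
- nHDI is a predefined index. Making a trimmed version the main score would fit the outcome to the intervention and would hide a real rise in cheese or red meat.

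All of this stands. It limits the size of the problem and argues for keeping the 14-item score, but it does not remove the conflict. The diary offered as mitigation in Section 3.3 does not resolve it either, because only the QDP group completes it.

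A reader might go further and infer that better adherence under QDP will push nHDI up and reverse the between-arm result. The documents do not support that. Both arms receive the same recommendations (Section 2.4), and nothing says which List A foods women will choose. Nor does cheese carry special weight: all 14 items share the same 0–2.0 scale.

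**Conclusion.** The conflict is real and undisclosed: two of 14 nHDI items are scored against foods that the tested protocol names as recommended. Adherence met through those foods can offset part of the List B gain and, in some scenarios, all of it. The illustrative net change for an adherent woman runs from about −6 to about +2 points on the 0–100 scale.

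The item overlap is certain, apart from reading red meat as covering beef, lamb and pork, which is ordinary usage. The point values are less firm. They rest on linear rescaling to 28, on the matching of diary and questionnaire categories, and on assumed starting diets. They also assume that the answers fully reflect the diet at follow-up. The questionnaire asks about the past 12 months, so an answer at six months may show less of the shift. The average shift in the trial cannot be derived from the documents.

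Within-arm change in nHDI is affected directly. The between-arm contrast is affected only so far as adherence through cheese or red meat differs between the arms.

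**What to change.** Keep the predefined 14-item nHDI as planned. In Section 2.12, before any data are analysed:

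- Pre-specify, as a sensitivity analysis, a 12-item nHDI that omits cheese and red meat, rescaled to 0–100 (maximum sum 24 under linear scoring). If nHDI enters the definition of high diet quality, repeat that model with the 12-item score.
- Report the cheese and red meat frequencies separately by arm at each visit, so that a real rise stays visible.
- State in Section 3.3 that two nHDI items run against the List A recommendations, and that the index and the lists must be read together.

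The cost is one scoring line and a short table, from item data already collected. The small downside is an extra score that is not comparable with published nHDI values, which is why the standard score stays. The change concerns scoring and reporting only; no dietary rule is proposed.

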### 2.6. Other Lifestyle Factors 

Self-reported data related to physical activity, time spent in front of a screen, and sleep duration (over the 12 last months), as well as smoking status will also be collected with the KomPAN questionnaire [30,31]. 

Physical activity in leisure time will be determined by choosing one of three categories: low (sitting, watching TV, reading, light housework, walking less than 2 h a week), moderate (walking, cycling, moderate exercise, working at home/garden, or other light physical activity performed 2–3 h/week) or high (cycling, running, gardening, and other sports/recreational activities requiring physical effort over 3 h/week). Physical activity at work will be determined by choosing one of three categories: low (more than 70% of time spent sedentary), moderate (about 50% of time spent sedentary and 50% active), or high (about 70% of time spent active or physical labor of high intensity). Screen time, defined as time spent watching TV or using computer/tablet (including work), will be determined by choosing one of six categories: <2 h, 2 to <4 h, 4 to <6 h, 6 to <8 h, 8 to <10 h, 10 h or more. Sleep duration during weekdays will be determined by choosing one of three categories: ≤6 h/day, >6 to <9 h/day, or ≥9 h/day. The same categories will be chosen for sleep duration during the weekend. Smoking status will be collected for the past and present (yes, no), and dichotomous categories will then be created: (i) non-smoker or past smoker, (ii) current smoker.

### 2.7. Quality of Life (QoL) 

To assess QoL, a thyroid-specific questionnaire (ThyPRO) in a Polish version (ThyPROpl) will be applied [32]. There is substantial evidence for the clinical validity and reliability of the questionnaire in patients with mild thyroid disorders [33,34]. The ThyPRO consists of 84 items summarized in 13 scales as well as a single item measuring the overall impact of thyroid disease on QoL within the last four weeks. The questionnaire covers physical symptoms specifically relevant to thyroid diseases (e.g., symptoms of hyperthyroidism and goitre) and non-specific aspects of high importance to patients with thyroid diseases (e.g., fatigue). Responses for each item will be scored with points on a five-point Likert scale as follows: ‘not at all’ (0 points), ‘a little’ (1 point), ‘some’ (2 points), ‘quite a bit’ (3 points), and ‘very much’ (4 points). The average score of items in a scale will be divided by four and multiplied by 100 to yield 13 scales ranging from 0 to 100 points [32,33], with higher point scores indicating a worse quality of life related to each scale.

### 2.8. Nutrition Knowledge and Sociodemographic Factors

Nutrition knowledge will be assessed with the KomPAN questionnaire [30,31]. Participants will be asked to provide answers (true/false/unsure) to the set of 25 statements; 1 point will be assigned for every correct answer and 0 points will be assigned for the wrong answer or ‘unsure’. All points will be summarized to express nutrition knowledge score (range 0–25 points). 

Data regarding sociodemographic variables will be obtained with the KomPAN questionnaire. Age (in years) will be recorded. The following variables will be collected using closed structured questions: place of residence (village; town <20,000 inhabitants; town 20,000 to 100,000 inhabitants; city over 100,000 inhabitants), level of education (primary; lower secondary; higher secondary; higher), financial situation (below average; average; above average), and household situation (we live very modestly; we live modestly; we live normally; we live relatively wealthy; we live very wealthy – all categories with detailed written explanation).

### 2.9. Adiposity Markers 

The measurements of body weight (kg; with electronic digital scale SECA 799), height (cm; with a portable stadiometer SECA 220), waist circumference (WC, cm; with a stretch-resistant tape SECA 201) will be taken. Body fat (BF, %) and skeletal muscle index (SMI, %) will be assessed using the bioelectrical impedance analysis (BIA) method (with the body composition analyzer SECA mBCA 525). All measurements will be taken in light clothing and without shoes according to the International Standards for Anthropometric Assessment (ISAK) guidelines [35]. Body mass index (BMI, kg/m^2^) and waist-to-height ratio (WHtR) will be calculated. Central adiposity (central obesity) will be identified as WHtR ≥0.5 [36] or WC ≥80 cm (ethnic- and gender-specific threshold) [37]. General adiposity will be identified with body mass index (overweight BMI = 25–29.9 kg/m^2^, obesity BMI ≥30 kg/m^2^) or body fat percentage (obesity gender-specific threshold: BF >33%) [38,39,40]. For a comprehensive interpretation of excessive body mass, which may result from excessive body fat mass and/or high skeletal muscle mass, low skeletal muscle index will be identified as SMI <22% (gender-specific threshold) [41]. 

### 2.10. Thyroid Function Tests (TFTs) and Metabolic Parameters

The following tests will be applied to monitor thyroid function: serum concentration of thyrotropin (TSH), free thyroxine (FT4), free triiodothyronine (FT3), serum auto-antibodies against thyroid peroxidase (TPOAb), and thyroglobulin (TgAb) [4,26]. TFTs results will be collected from the respondents (from different laboratories) and will be interpreted using laboratory thresholds to find abnormalities.

Office measurements (i.e., taken at a dietetic lab) of the systolic (SBP) and diastolic (DBP) blood pressure (mmHg; with an electronic shoulder manometer and an automatic analyzer of the ankle brachial index MESI ABPI MD by the oscillometric technique) will be taken [42,43]. Serum fasting glucose (FBG), triglycerides (TG), and total cholesterol (TC) will be measured in capillary blood (with an Accutrend PLUS analyzer, Roche Diagnostics). Metabolic parameters will be determined as elevated if FBG ≥100 mg/dL, TG ≥150 mg/dL, TC ≥200 mg/dL [44,45] and at least one component of blood pressure is elevated (SBP ≥130 or DBP ≥85 mmHg) [44]. 

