### 2.2. Participants Selections

The participants will be recruited for the study through ads in the press, via the Internet and by e-mail invitation between October and December 2019. Approximately 140 women with HT are expected to respond to the invitation letter (describing the details of the planned trial) and will be screened for eligibility (Figure 1). All visits for data collection will take place at the Department of Human Nutrition (Center of Gastronomy with Dietetics and Food Bioassessment), Faculty of Food Science, University of Warmia and Mazury in Olsztyn. The trial starts in winter months, and all subjects will be advised to continue their long-term vitamin D supplementation. 

To take part in the study, the participants have to be prior diagnosed as having HT according to the American Thyroid Association guidelines [26] and have a medical certificate for levothyroxine or other thyroid hormone treatment (e.g., levothyroxine plus liothyronine). The participants will be required to show a medical diagnosis with thyroid ultrasonography and the results of thyroid function tests carried out no later than two months before enrolment. Detailed inclusion and exclusion criteria are presented in Table 2. Information collected at the interview, which not will be used as including/excluding criterion, is the age at which HT was diagnosed, the use of dietary supplements in the past, the dose of levothyroxine or other thyroid hormones in current treatment, and hormone status (menstruating: yes, no, irregular). Elevated serum auto-antibodies against thyroid peroxidase and thyroglobulin will be recorded but will not be used as excluding criterion.

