### 2.12. Statistical Analysis

Categorical variables will be presented as a sample percentage (%) and continuous variables will be presented as means with a 95% confidence interval (95%CI) or medians with an interquartile range (IQR) for variables with normal or non-normal distribution, respectively. To assess the impact of dietetic counseling and verify the differences between the experimental and the control group, two-tailed tests will be applied; *p*-values < 0.05 will be considered significant. 

The normality of variable distribution will be verified with a Kolmogorov–Smirnov test before the statistical analysis. For continuous variables, e.g., diet quality scores, AdhS, scores of QoL, nutrition knowledge score, TFTs, markers of adiposity, metabolic parameters, and changes after a six-month follow-up with respect to baseline will be verified with a T-test for dependent samples or a Mann–Whitney test, for variables with normal or non-normal distribution, respectively. For categorical variables, logistic regression modeling will be applied to determine the chance of the occurrence of high diet quality, high AdhS, high QoL, as well as low adiposity and elevated metabolic parameters. The odds ratios (ORs) and 95% confidence intervals (CIs) will be calculated. The significance of ORs will be verified with Wald’s statistics. A crude model and models with an adjustment for confounders will be created. All analyses will be performed with Statistica software (version 13.3 PL; StatSoft Inc., Tulsa, OK, USA; StatSoft, Krakow, Poland).

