## Figures and Tables

**Figure 1 ijerph-16-04841-f001:**
[figure not shown]
Sample collection chart.

**Table 1 ijerph-16-04841-t001:** Timetable of data collection.

Timing	Activities	Group	
		Experimental	Control
T0 visit (enrolment)	Eligibility screening; Written informed consent; Assignment to the experimental or control group.	✕	
T1 visit (baseline)	Data collection of diet quality and other lifestyle factors, quality of life, nutrition knowledge, sociodemographic factors.	✕	✕
	Measurements of adiposity, metabolic parameters, and thyroid function.	✕	✕
	Dietetic counseling.	QDP	CDC
Between visits	Home collection of dietary data with self-monitoring.	✕	
T2 visit (1-month follow-up)	Dietetic consultation to boost compliance with dietary guidelines.	✕	✕
	Data collection of diet quality and other lifestyle factors, quality of life.	✕	✕
	Measurements of adiposity and metabolic parameters.	✕	✕
Between visits	Home collection of dietary data with self monitoring.	✕	
T3 visit (6-month follow-up)	Data collection of diet quality and other lifestyle factors, quality of life, nutrition knowledge.	✕	✕
	Measurements of adiposity, metabolic parameters, and thyroid function.	✕	✕

QDP—a qualitative dietary protocol; CDC—conventional dietetic counseling.

**Table 2 ijerph-16-04841-t002:** Participant eligibility criteria. BMI: body mass index.

**Inclusion Criteria**: women age >18 and <60 years; prior diagnosed Hashimoto thyroiditis: hypothyroidism or subclinical hypothyroidism; medical certificate for levothyroxine treatment or other thyroid hormones; agreement to take part in the study;

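### Thyroid tests come from different laboratories and are read against each laboratory's thresholds, but Section 2.12 tests them and their six-month change as continuous variables with no stated laboratory-referenced scale

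*Protocol article*

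**What the plan says.** Section 2.10 names five thyroid tests: TSH, FT4, FT3, TPOAb and TgAb. On their source and their reading it says "TFTs results will be collected from the respondents (from different laboratories) and will be interpreted using laboratory thresholds to find abnormalities". In the same section, glucose, triglycerides and total cholesterol are measured on one named analyser.

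Section 2.12 lists among its continuous variables "nutrition knowledge score, TFTs, markers of adiposity, metabolic parameters, and changes after a six-month follow-up with respect to baseline", to be tested with a "T-test for dependent samples or a Mann–Whitney test" according to normality. The binary outcomes for logistic regression are diet quality, adherence, quality of life, adiposity and metabolic parameters. Abnormal thyroid tests are not among them.

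On timing, Section 2.2 requires a woman to show "the results of thyroid function tests carried out no later than two months before enrolment". Table 1 lists "Measurements of adiposity, metabolic parameters, and thyroid function" at T1 (baseline) and again at T3 (six months).

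**The concern.** Reading a result against its own laboratory's threshold is sensible when results come from several laboratories, because it does not require raw values to be comparable. A continuous analysis does require that, unless the values are first put on a common scale. The plan pairs a multi-laboratory source with continuous testing and names no such scale. The one reading that Section 2.10 describes, normal or abnormal, has no listed analysis.

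What is at stake is the interpretation of thyroid function at six months. A woman's recorded change may be partly a change of assay. There is also an ambiguity about the baseline value: it could be the result shown for eligibility or a separate one at T1.

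**Working it through.** The documents give no figure for the thyroid tests, so there is no stated number to reproduce. The check has three parts.

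**1. The sections side by side**

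| Item | Where | What is stated |
|---|---|---|
| Source | 2.10 | participants' own results, several laboratories |
| Reading | 2.10 | against laboratory thresholds (categorical) |
| Analysis | 2.12 | continuous values and six-month change |
| Abnormality as an outcome | 2.12 | not listed |
| Timing | 2.2 | two-month limit on the result shown at entry |
| Timing | Table 1 | thyroid function at T1 and T3 |

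Taken literally, the phrase in Section 2.2 asks for a result at least two months old; the opposite is probably meant. No section says whether this result is also the T1 value.

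**2. Effect on the between-arm comparison (illustration)**

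- From Section 2.11: 50 per arm and 20% drop-out, so 50 × (1 − 0.20) = 40 completers per arm; 5% level and 80% power. Section 2.12 makes the tests two-sided.
- Assumed: the SD of the true change is 1 (the unit); laboratory offsets are additive with SD r; a fraction f of women change laboratory.
- A woman who keeps her laboratory has the same offset twice, and it cancels. For a woman who switches, the change gains the difference of two independent offsets, with variance 2r².
- SD of the observed change = √(1 + 2fr²).
- Difference detectable with 80% power without laboratory noise: (1.960 + 0.842) × √(2/40) = 0.626.
- Power = Φ(0.626 / (SD × √(2/40)) − 1.960).

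Worked example, r = 0.5 and f = 0.5: SD = √1.25 = 1.118, and power is 71%.

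| r | f = 0 | f = 0.25 | f = 0.5 | f = 1 |
|---|---|---|---|---|
| 0.25 | 80% | 79% | 78% | 75% |
| 0.5 | 80% | 75% | 71% | 63% |
| 1.0 | 80% | 63% | 51% | 37% |

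Allocation is random, so the expected difference between arms due to offsets is zero in every cell. The loss is one of precision.

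**3. Effect on the within-arm paired test (illustration)**

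Randomisation does not protect a before–after test. Suppose assay changes or timing move the mean change in an arm by s SDs of the change, with no dietary effect. With n = 40 the rejection rate is Φ(s√40 − 1.960) + Φ(−s√40 − 1.960).

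| s | Rejection rate (nominal 5%) |
|---|---|
| 0.1 | 10% |
| 0.2 | 24% |
| 0.3 | 48% |
| 0.5 | 89% |

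This needs a net shift in one direction. Offsets that average to zero across women add noise here too, but no bias.

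**The case against.** The strongest reply has three parts.

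- **Thyroid tests carry little weight in this trial.** They are not in the aims of Section 1.1, the hypotheses or the sample size of Section 2.11. The abstract lists thyroid function only among the data collected. This stands and limits the importance of the point.
- **A condensed article need not give a same-laboratory rule, a date window or form fields, and Section 2.12 never says that the change is on the raw scale.** This also stands, so the absence of those details is not the fault. What remains is the mismatch between two stated elements: several laboratories with threshold reading, and continuous testing.
- **The size is entirely assumed.** This is correct. The documents give neither between-laboratory variation nor a switching rate, and the table above starts at no loss at all.

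A reader might infer three stronger things that the documents do not support. The first is that baseline results are up to two months old, so that the change spans about eight months. Section 2.2 sets its limit for the result shown at entry, Table 1 lists thyroid function at T1, and nothing says that they are the same result or when the six-month sample is drawn. The second is that laboratory differences systematically favour one arm. Allocation is random and nothing links the choice of laboratory to arm; chance imbalance is already covered by the 5% level. The third is that some of the five tests are worse affected than others. The documents give no basis for ranking them.

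**Conclusion.** The point holds as a moderate one. As written, the plan lets assay differences into the thyroid values and changes that it tests, while the threshold reading that would cope with several laboratories has no listed analysis. Between arms the cost is lost precision. In the within-arm paired test, bias is possible if assay or timing shifts run in one direction. Women who keep one laboratory contribute no additive offset to the change, although a proportional calibration difference would still rescale a raw change.

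The size is unknown. The results above rest on 40 completers per arm, additive independent offsets and assumed values of r, f and s; they run from negligible to substantial. Separately, Section 2.2 and Table 1 need to be reconciled on which result is the baseline.

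**What to change.** - **Collection.** Ask each woman to use the same laboratory for T1 and T3, within a stated window of each visit. Record laboratory, unit and reference limits with every result.
- **Baseline.** State in Section 2.2 and Table 1 whether the eligibility result serves as the T1 value. If the intended limit is that results be no more than two months old at enrolment, say so in those terms.
- **Main analysis in Section 2.12.** Compare the arms on the six-month value expressed relative to that laboratory's limits, adjusted for baseline on the same scale. Examples are the log ratio to the upper limit for TSH, TPOAb and TgAb, and position within the reference range for FT4 and FT3. Where laboratory and limit stay the same, the log ratio leaves the log change unaltered; its value is for women who switch and for comparing levels between women.
- **Analysis set.** Keep all randomised women with data. Dropping those who changed laboratory would be a post-randomisation exclusion, so restrict to same-laboratory women only as a sensitivity analysis.
- **Categorical outcome.** Add abnormal thyroid tests, by laboratory threshold, to the logistic outcomes.

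The cost is a minor burden on participants, a few extra data fields and a short addition to Section 2.12. The collection steps must be in place before the samples are drawn, because a change of laboratory cannot be undone afterwards.
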